## Abstract

**Background:**

Coronary Artery Bypass Graft operation for ischemic heart disease provides improved quality of life and, in some patients, prolonged survival. Concern has, however, been raised about complications that may be related to the use of cardiopulmonary by-pass (CPB) and aortic cross-clamping. It has been hypothesized that when coronary artery by-pass grafting is performed without the use of CPB, the rate of serious complications is reduced.

**Methods/Design:**

The trial is designed as an open, randomized, controlled, clinical trial with blinded assessment of end-points. Patients at or above 70 years of age, referred for surgical myocardial revascularisation, are included and randomised to receive coronary artery by-pass grafting either with or without the use of CPB and aortic cross-clamping. Follow-up is performed by clinical, biochemical, electrocardiographic, and angiographic data that are evaluated by independent committees that are blinded with respect to the result of the randomisation. End points include mortality, stroke, myocardial infarction, graft patency, quality of life, and cost-effectiveness. The trial is performed in four different Danish, cardiac surgery centres.

**Trial registration:**

ClinicalTrials.gov NCT00123981

## Background

Conventional Coronary Artery By-pass Grafting (CCABG) using CPB has for decades been applied to obtain myocardial re-vascularisation and, hence, improved quality of life and survival. It does, however, bear a risk of death, stroke, myocardial infarction and other serious complications.

During recent years, an equivalent operation performed on the beating heart without cardiopulmonary bypass (Off-pump Coronary Artery By-pass Grafting, OPCAB) has gained popularity helped by the advent of mechanical stabilization devices and improved surgical techniques. Observational studies suggest that this technique is associated with a lower incidence of stroke, per operative arrhythmias and even mortality than conventional CCABG [1]. This is especially the case in elderly patients and patients with significant co-morbidity [2-4].

Only few randomised, controlled trials have been conducted [5-9] and most of these included mainly or only low-risk, relatively young patients. These studies have documented the safety and efficacy of OPCAB compared with CCABG, but none of the trials has had the statistical power to determine whether the rate of serious complications is lower after OPCAB operations. In contrast to earlier findings [5], one recent study found graft patency to be significantly lower after OPCAB than after CCABG operations [9].

We find that there is a need of a larger scale randomised trial to compare the results of CCABG and OPCAB operations, especially in elderly patients.

### Aims

Primarily, to compare the incidence of death, stroke and myocardial infarction after CCABG and OPCAB procedures in a population of elderly patients. Secondly, to compare quality of life and graft patency, and cost-effectiveness after CCABG and OPCAB.

## Design

An open, randomised Danish multicentre trial of patients 70 years of age or above, admitted for surgical, first time myocardial re-vascularisation. The design involves blinded evaluation of outcome measures and interim analyses.

### Approval to start

Patients will be enrolled in the study based upon written informed consent in accordance with Helsinki Declaration II. The study plan has been approved by the local ethical committees and the national ethical committee.

### Trial surgeon's requirements

Before being certified to participate, the surgeons must at least independently have performed 25 CCABG and 25 OPCAB procedures each procedure including anastomoses to the marginal tbranches of the left coronary artery. This territory is the most challenging to graft. Therefore, all surgeons fulfilling this criterium will first have performed a significant number of other coronary artery by-pass operations and have an intermediate level of experience reflecting common clinical situations. Based upon these criteria and on documented results of the operations, surgeons must also be certified by the ethical and safety data committee.

### Inclusion criteria

Patients age seventy years or above admitted for first time coronary artery by-pass operation without other planned surgical procedure.

### Exclusion criteria

- Patient not willing to participate in the study

- The patient cannot understand given information or answer questionnaires relevantly due to intellectual or linguistic deficiency

- Preoperative knowledge that aortic cross clamping is not safe due to calcification e.g. from CT-scan.

- Preoperative cardiac conditions demanding CPB.

- Re-do cardiac surgery.

- Acute operation defined as patient requiring operation before the beginning of the next working day after first being presented to the surgeon.

- Any other reason why the operating surgeon does not believe that the patient can be operated safely either using CPB or without CPB.

- Inclusion in study not possible for logistic reasons

### Consent and inclusion procedure

After written and oral information is given by the project nurse at the ward at time of admission for coronary artery by-pass grafting, the patient has to give oral and written consent.

### Randomisation

The operating surgeon enters patients in a central database accessed by the internet. Before being able to randomise, the surgeon has to enter a preoperative plan including which coronary arteries are to be grafted, the conduit type and whether a single, sequential, or y-graft is planned. Having done this the patient is subsequently randomised either to OPCAB or CCABG by the on-line system

### Blinding

For practical end ethical reasons, neither the patient nor doctors or nurses are blinded with respect to the type of treatment used. Events will, however, be evaluated by an independent committee that will be blinded.

### Sample size

900 patients including 450 patients randomised for OPCAB and 450 randomized for CCABG.

### Power calculations

The incidence of the primary, combined end-point is estimated to be 8%. This estimate is based on literature as well as on historical data from the participating centres from the period 2001–2003. Based on earlier, observational studies of elderly patients undergoing coronary revascularisation [2,3], we hypothesize that this incidence can be reduced to 4% by avoiding cardiopulmonary by-pass. With a margin of 0.5% in risk difference a test of non-inferiority of OPCAB compared to CCABG based on 900 patients will have a statistical power of 82%.

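### The only stated power (82%) is for a non-inferiority test that assumes OPCAB halves the risk; the difference test in the Analysis section has about 71–72% power

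*Protocol article*

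**What the plan says.** All references are to the protocol article.

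- **Power calculations.** The planning rate is given first: "The incidence of the primary, combined end-point is estimated to be 8"%. Then, from observational studies, "we hypothesize that this incidence can be reduced to 4% by avoiding cardiopulmonary by-pass". The test is named next: "With a margin of 0.5% in risk difference a test of non-inferiority of OPCAB compared to CCABG". Its power at the planned total is put at 82%, and no other power is given.
- **Sample size.** "900 patients including 450 patients randomised for OPCAB and 450 randomized for CCABG".
- **Analysis.** Groups are compared by Kaplan-Meier plots and the log-rank test, by intention to treat. There is one interim analysis at half recruitment, with significance at p below 0.5% there and below 4.8% at the end, to keep an overall 5% level. Neither non-inferiority nor the 0.5-point margin appears. The level is not called one-sided or two-sided.
- **Framing.** The abstract's background reports the hypothesis that without cardiopulmonary bypass "the rate of serious complications is reduced". The Background section says of earlier trials that "none of the trials has had the statistical power to determine whether the rate of serious complications is lower after OPCAB operations". The Aims section is neutral: it sets out to compare the incidence of the components.

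**The concern.** The power statement and the analysis plan describe different tests. One is non-inferiority with a margin. The other is a test of difference with p-value thresholds. The hypothesis in the same paragraph as the power figure is a reduction, which fits the difference test. So the trial's only power figure does not belong to its only stated test of the primary endpoint.

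The non-inferiority figure also depends on an unusual alternative. Non-inferiority power is usually quoted at equal risks; here it is quoted at a true 4-point advantage, to which the margin adds half a point. This matters in two ways. A reader may take 82% as the chance of detecting the halving of risk. And if the two techniques are truly equivalent, the trial would nearly always miss the margin, a result that could be misread unless the interval is shown beside it.

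**Working it through.** **Inputs.** CCABG risk 0.08, OPCAB risk 0.04 and margin 0.005 (Power calculations); 450 per arm (Sample size); overall level 5%, final level 4.8% (Analysis). Assumption: the level is two-sided, so non-inferiority is tested at one-sided 2.5%.

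**1. Reproduce the 82%.**

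SE = √(0.08×0.92/450 + 0.04×0.96/450) = 0.01578.

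Power = Φ((0.04 + 0.005)/SE − 1.960) = Φ(2.852 − 1.960) = Φ(0.892) = 81.4%.

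With a pooled SE it is 81.2%. Simulation gives 82.2%, or 81.9% with the interim analysis included. At one-sided 5% the result would be 88.6%, which does not match. The stated figure is therefore non-inferiority at one-sided 2.5%, with the full benefit assumed.

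**2. Power of a difference test at the same rates.**

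Power = Φ(0.04/0.01578 − z) = Φ(2.535 − z).

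| Method | Two-sided 5% (z = 1.960) | Two-sided 4.8% (z = 1.977) |
|---|---|---|
| Proportions, unpooled SE | 71.8% | 71.2% |
| Proportions, pooled SE | 71.5% | 70.9% |
| Log-rank, Schoenfeld | 74.7% | 74.1% |
| Fisher's exact | 67.4% | not computed |

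For the log-rank row, expected events = 450×0.08 + 450×0.04 = 54, and the hazard ratio is ln(0.96)/ln(0.92) = 0.490. Then √54/2 × |ln 0.490| = 2.624, and Φ(2.624 − 1.960) = 74.7%. Freedman's log-rank formula gives 71.2% at the 5% level. Simulation of the two-look design (0.5% and 4.8%, pooled test of proportions) gives 72.0%. For scale, 80% power for this difference by the pooled test of proportions at two-sided 5% needs 553 per arm, 1106 in total.

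**3. Non-inferiority power at other true OPCAB risks** (CCABG 8%, one-sided 2.5%). Power = Φ((0.08 − p + 0.005)/SE(p) − 1.960).

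| True OPCAB risk p | SE(p) | Power |
|---|---|---|
| 4% | 0.01578 | 81.4% |
| 5% | 0.01640 | 56.9% |
| 6% | 0.01700 | 31.2% |
| 7% | 0.01756 | 13.4% |
| 8% | 0.01809 | 4.6% |

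At equal risks the margin is 0.005/0.01809 = 0.28 of a standard error, and the 95% half-width is 1.96×0.01809 = 3.5 points against a 0.5-point margin. Power of 80% there would need (1.960 + 0.842)² × 2×0.08×0.92/0.005² ≈ 46,200 per arm.

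**4. Observed difference needed to meet the margin.** With the SE at 8% versus 4% and the final level: 1.977×0.01578 − 0.005 = 0.026, or 2.6 points in favour of OPCAB. The SE depends on the observed rates. With CCABG observed at 8%, solving 0.08 − p + 0.005 = 1.977×SE(p) gives p ≈ 5.2%, a gap of about 2.8 points. The threshold is thus roughly 2.6 to 2.8 points.

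**The case against.** **The figure is correct and labelled.** The sentence names the test, the margin, the rates and the number of patients, and the arithmetic holds. This stands. A reader might infer that 82% is a calculation error; it is not. What is wrong is its relation to the Analysis section.

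**The objective is not plainly superiority.** The Aims section says only that incidences are compared, and the Background sentences describe a general hypothesis and the limits of earlier trials. This also stands. Superiority is a fair reading of the hypothesised reduction and the log-rank test, but the article does not declare it primary. The review can ask for a choice but cannot make it.

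**The 71–72% depends on the test and on sidedness.** It does: two-sided methods range from about 67% to 75%. A difference test at one-sided 5% would have about 81% power (Φ(2.535 − 1.645) = 81.3%), close to the printed figure. But the article attaches 82% to a non-inferiority test with a margin, and that test matches at one-sided 2.5%, so a two-sided 5% level is the likelier reading.

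**Non-inferiority is not impossible at equal risks.** Correct. A reader might infer that it is unattainable, but power is about 5%, not zero.

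**Nothing says a missed margin will be read as inferiority.** True; the Analysis section has no margin rule at all. The risk of misreading is a reason to report the interval, not a fault already in the text.

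**A condensed article may leave detail out.** It may, but here the two sections printed in it disagree on the type of test. That is a conflict in the text, not an omission.

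**Conclusion.** The point holds as a mismatch between the Power calculations and Analysis sections. The 82% is valid for non-inferiority with a 0.5-point margin when OPCAB truly halves the risk from 8% to 4%. For the planned difference test at the same rates, power is about 71–72% by proportions, so the chance of missing a true halving is about 28–29% rather than 18%. If the risks are equal at 8%, non-inferiority would be shown about 5% of the time, and an observed advantage of roughly 2.6 to 2.8 points would be needed to meet the margin.

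These results rest on the stated rates, 450 analysed per arm, normal approximations and a two-sided level, which the article does not state. The documents do not support saying that the power was miscalculated, that non-inferiority cannot be shown, or that superiority is the declared primary objective.

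**What to change.** 1. Reconcile the Power calculations and Analysis sections on which hypothesis is primary, and state whether the level is one-sided or two-sided. If non-inferiority is kept, the Analysis section needs the margin and a confidence-limit rule.
2. Restate the power, for example: *With 450 patients per arm, power is about 71% (two-sided 4.8% final level) to show a difference for 8% versus 4%. The non-inferiority test with a 0.5-point margin has about 81–82% power only if OPCAB truly halves the risk, and about 5% if the risks are equal.*
3. Commit to reporting the 30-day risk difference with its confidence interval, so that a missed 0.5-point margin is not read as evidence of inferiority.

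The cost is rewording and a less favourable power statement. The sample size does not change.

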### Operations and anaesthesia

The coronary artery by-pass operations are performed either with or without the use of CPB according to the result of randomisation. Operative protocols are used to limit the variations of technique, although leaving some room for variations according to the discretion of the individual surgeon and the tradition of each participating unit. The operative protocols are given in Appendix 1. When judged vital for the outcome of the patient, conversion from one group to the other can be decided by the operating surgeon at any time during the operation. Equally, anaesthetic protocols are followed in order to limit the variations between the units (Appendix 2)

### Postoperative treatment

Postoperative treatment of included patients with acetyl salicylic acid, clopidogrel, angiotensin converting enzyme inhibitors, diuretics, amiodarone and heparin will be performed according to detailed protocols (Appendix 3)

In case deviation from the protocol is deemed necessary, such altered strategies are to be duly noted and accounted for.

### Follow-up

*At preoperative conference: *Evaluation of whether the patient meets the inclusion and/or exclusion criteria. All patients above 70 years who are to have a sole by-pass operation are registered. If the patient is not included in the project, the reason is noted.

*Day one: *The day the patient is admitted to the hospital for operation. Informed oral and written information and consent. Questionnaires are answered.

*Day two: *Randomization. CCABG or OPCAB are performed according to randomization.

*Day 31: *Telephone contact and ECG. Evaluation of primary end-point.

*Six months postoperatively: *Coronary angiography. Clinical control and questionnaire.

*Three years postoperatively: *Clinical control and questionnaire.

During follow-up the patients will be followed up through unambiguous record linkage with population-based registries by using the civil registry number, which is a unique identification code given to every person residing in Denmark at birth or upon immigration. Information on death will be obtained from the Civil Registration System, which keeps electronic records on all changes in vital status, including change of address, date of emigration, and date of death for the entire Danish population.

Information on hospitalizations for myocardial infarction and stroke will be obtained from The National Registry of Patients, which retains key information on all patients discharged from non-psychiatric hospitals in Denmark since 1977, including outpatient diagnoses, and patients dying during their admission. The files of the registry include information on the civil registry number of the patient, date of discharge, and up to 20 discharge diagnoses, assigned exclusively by the physician at discharge according to the Danish version of the International Classification of Diseases, 10th revision (ICD-10) thereafter [10]. Full medical records including results of paraclinical examinations and tests will be retrieved and reviewed according to standardized internationally accepted criteria for all patients who die and/or are registered with a discharge diagnosis of acute myocardial infarction or stroke during the study period. All data will be presented for the independent monitoring committee.

### Primary endpoint

A combined end-point of death + stoke + myocardial infarction within 30 days postoperatively. Definitions of end-points will be according to appendix 4.

### Secondary endpoints

a) A combined end-point of death + stoke + myocardial infarction during follow-up

b) Patency of by-pass grafts assessed by coronary angiography 6 months after the operation.

c) Total mortality and cardiac mortality during follow-up.

d) Need of new intervention for cardiac angina during follow-up.

e) Quality of life assessed by MOS SF-36 and EuroQol questionnaires 6 months and 3 years after the operation.

f) Total hospital costs and costs of public care provided 6 months and 3 years after the operation and difference in costs per quality adjusted life year.

### Analysis

Kaplan-Meier plots will be used for graphic comparisons between groups and log- rank test for numerical comparison. Data analysis will be performed in accordance with the principle of intention-to-treat. An interim analysis will be performed for monitoring the accumulating data during the planned study period, i.e., after half of the patients have been recruited. The O'Brien-Fleming approach will be used in these analyses. At the interim analysis a p-value below 0.5% will be considered significant, while a p value below 4.8% will be considered significant after conclusion of the study. In this manner, a 5% level of significance is sustained. For the 6 months and 3 years data, Kaplan-Meier plots will be used for graphic comparisons between groups and log- rank test for numerical comparison.

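### The stated 82% power belongs to a non-inferiority test on a 0.5-point risk-difference margin, but the Analysis section states a log-rank test with p-value cut-offs, which uses no margin and has about 72% power

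*Protocol article*

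**What the plan says.** The primary endpoint is a composite over a fixed period: death, stroke or "myocardial infarction within 30 days postoperatively" (Primary endpoint). The Sample size section gives "900 patients including 450 patients randomised for OPCAB and 450 randomized for CCABG".

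The Power calculations section assumes a composite incidence of 8% and adds: "we hypothesize that this incidence can be reduced to 4% by avoiding cardiopulmonary by-pass". Its power sentence begins "With a margin of 0.5% in risk difference a test of non-inferiority of OPCAB compared to CCABG based on 900 patients" and ends with 82%. This is the only power statement in the article and the only place where non-inferiority or a margin appears.

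For the analysis, the article says "Kaplan-Meier plots will be used for graphic comparisons between groups and log- rank test for numerical comparison". The decision rule is: "At the interim analysis a p-value below 0.5% will be considered significant, while a p value below 4.8% will be considered significant" at the end of the study. The Analysis section mentions no margin, risk difference, confidence limit or non-inferiority criterion. The Aims section says only that the incidences will be compared.

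**The concern.** The test that was powered and the test in the Analysis section address different hypotheses. The powered test asks whether the data exclude an OPCAB risk that is 0.5 points or more above the CCABG risk. A standard log-rank test asks whether the event-time distributions differ at all. It contains no margin and does not estimate an absolute risk difference.

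Two consequences follow if the Analysis section is applied as it stands. First, the 82% does not describe the test whose p-value decides the result. Second, some trials would satisfy the non-inferiority criterion and still be recorded as not significant, because the written rule gives the margin no role. A non-significant log-rank result could not fill that gap, since failing to find a difference does not exclude a difference of a given size.

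**Working it through.** **Inputs.** n = 450 per arm (Sample size); CCABG risk 8%, OPCAB risk 4%, margin 0.5 points, stated power 82% (Power calculations); p-value limits 0.5% and 4.8%, overall 5% (Analysis). The article does not state sidedness. I assume two-sided 5% for a difference test, hence one-sided 2.5% for non-inferiority.

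**Step 1: reproduce the stated power.**

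SE = √(0.08×0.92/450 + 0.04×0.96/450) = √(0.112/450) = 0.01578.

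Power = Φ((0.04 + 0.005)/0.01578 − 1.960) = Φ(0.892) = 81.4%.

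At the final level (one-sided 2.4%, z = 1.977) it is 80.9%. Variants at one-sided 2.5% give 81.2% (pooled variance), 80.8% (Farrington-Manning) and 82.2% (simulation). One-sided 5% gives 88.6%. So 82% fits the non-inferiority test at one-sided 2.5%.

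**Step 2: power of a test of no difference, same inputs.**

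| Method | two-sided 5% | two-sided 4.8% |
|---|---|---|
| Two proportions, pooled variance under the null | 71.5% | 70.9% |
| Log-rank, Schoenfeld formula | 74.7% | 74.1% |
| Log-rank, simulated (6,000 trials) | 72.1% | 71.6% |

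With unpooled variance: Φ(0.04/0.01578 − 1.960) = Φ(0.575) = 71.8%.

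Schoenfeld: expected events = 450×(0.08 + 0.04) = 54; hazard ratio = ln(0.96)/ln(0.92) = 0.490; power = Φ(√(54/4)×|ln 0.490| − 1.960) = Φ(0.664) = 74.7%.

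The range is therefore 71-75%, with simulation near 72%. A difference test with 82% power would need about 582 per arm, 1,164 in total.

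**Step 3: how often the two criteria disagree.** One million trials were simulated at 8% vs 4%, with a two-proportion z-test standing in for the log-rank test and both criteria at z = 1.96:

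- margin met: 82.2%
- significant difference in favour of OPCAB: 72.3%
- margin met without a significant difference: 9.9%

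Since 82.2 − 9.9 = 72.3, the simulated trials significant in favour of OPCAB also met the margin.

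**Step 4: what a non-significant result shows.** Suppose both risks were 8%, which is not a design assumption. About 100 − 4.8 = 95.2% of trials would then be non-significant at the final level. The margin would be met in Φ(0.005/√(2×0.08×0.92/450) − 1.960) = Φ(0.276 − 1.960) = 4.6% (one-sided 2.5%). Non-significance and non-inferiority are thus very different findings.

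**Step 5: the alpha split.** Limits of 0.5% at half the information and 4.8% at the end give an overall two-sided level of 4.99%. The article's 5% claim is sound for a two-sided difference test.

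**The case against.** **The non-inferiority test is named.** The Power calculations section states the test, its scale and its margin. The article is condensed, and an analysis plan that is not shown may supply the confidence-interval method. This stands, so a reader who infers that non-inferiority is never tested goes beyond the document. It does not remove the mismatch: the Analysis section fixes a test and significance limits, and these belong to another hypothesis.

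**The trial may be meant as a superiority trial.** The Abstract and the Power calculations section both hypothesise a reduction, and the Aims are neutral. A log-rank test fits that reading. This also stands, and it means that the article does not establish non-inferiority as the primary question. On this reading the power sentence is what needs correcting.

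**The loss is limited.** A reader might infer that the trial cannot deliver the conclusion it was sized for. That is too strong. A significant result favouring OPCAB would in practice also exclude the margin, so the loss under the design assumptions is about 10 points of power. The 95.2% vs 4.6% contrast in Step 4 lies outside those assumptions, and nothing in the article says that p above 4.8% will be read as non-inferiority.

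**Sidedness.** If the 4.8% were one-sided, a difference test would have about 80.8% power, close to the stated figure. The article does not say that it is. The power sentence names non-inferiority, and that test would then have 88.3%, not 82%.

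**Conclusion.** The concern holds as a mismatch between two stated parts of the article. The 82% is about right for non-inferiority on a 0.5-point margin (81.4% recomputed). The log-rank test in the Analysis section has about 72% power (71-75% by method) under the same assumptions. At 8% vs 4%, about 10% of trials would meet the margin without a significant difference, and the written rule gives them no conclusion. A non-significant log-rank result would not show non-inferiority.

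This rests on the article's own risks and sample size, and on the assumption of two-sided 5% (one-sided 2.5% for non-inferiority). The sample-size arithmetic itself is not in error. The document leaves open which hypothesis is primary, and the sponsor has to settle that before unblinded results are seen.

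**What to change.** Choose one of two, and make the Power calculations and Analysis sections agree.

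**If non-inferiority is primary:** in the Analysis section, make the primary analysis the 30-day risk difference (OPCAB minus CCABG) with a two-sided 95.2% confidence interval at the final analysis, matching the 4.8% level. Declare non-inferiority if the upper limit is below +0.5 points. Only then test superiority (upper limit below 0), in fixed sequence and without further alpha. State which hypothesis the interim 0.5% level serves. Keep the Kaplan-Meier plots and log-rank test as supportive. The stated power then stands at about 81%.

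**If superiority is primary:** keep the difference test, remove the non-inferiority sentence from the Power calculations section and restate the power as about 71-75% for 900 patients.

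Either choice costs a few sentences, with no new data and no change in sample size. The second also means accepting openly a lower power than the article now states. The first calls for a word on how conversions between arms, which the Operations and anaesthesia section permits, bear on an intention-to-treat non-inferiority conclusion, because they can pull the arms together.

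### The general Kaplan-Meier prescription also covers cardiac mortality and new intervention, where censoring competing deaths makes the plotted risk modestly too high

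*Protocol article*

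**What the plan says.** The Analysis section of the protocol article names one time-to-event method and names it twice. The general statement is "Kaplan-Meier plots will be used for graphic comparisons between groups and log- rank test for numerical comparison". The section then repeats the method for the later time points: "For the 6 months and 3 years data, Kaplan-Meier plots will be used for graphic comparisons between groups", again with the log-rank test. It does not list the endpoints to which this applies and makes no exception.

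The Secondary endpoints section lists four outcomes of the time-to-event kind:

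- item a: "A combined end-point of death + stoke + myocardial infarction during follow-up"
- item c, which holds two: "Total mortality and cardiac mortality during follow-up"
- item d: "Need of new intervention for cardiac angina during follow-up"

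The population is described under Inclusion criteria: "Patients age seventy years or above admitted for first time coronary artery by-pass operation". The last scheduled contact in the Follow-up section is at three years ("Clinical control and questionnaire"). Deaths are captured for everyone: "Information on death will be obtained from the Civil Registration System". The same section provides for retrieval and review of the full medical records of all patients who die.

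**The concern.** Kaplan-Meier suits the composite and total mortality, because every death counts as an event. The other two endpoints differ. A patient who dies of a non-cardiac cause can no longer die of a cardiac one, and a patient who dies of any cause can no longer have a new intervention. Kaplan-Meier would treat these patients as censored, as though they could still have the event later. One minus Kaplan-Meier then estimates risk in a hypothetical setting without the competing deaths, and it lies above the proportion of real patients who have the event.

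In patients aged 70 or more followed for three years, some competing deaths must be expected. What is at stake is the description of 3-year risk for two secondary endpoints. A reader will take the curves as the chance of reintervention or cardiac death after each operation, and that chance would be somewhat too high. If mortality differs between the arms, the overstatement differs too, so the distance between two Kaplan-Meier curves need not equal the difference in actual risk.

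**Working it through.** **Figures in the plan.** The document gives no rate for cardiac mortality, new intervention or 3-year mortality, so there is no figure on this point to reproduce. Its one calculated figure, 82% power for the primary endpoint, does reproduce. With 450 per arm, 8% v 4% and a margin of 0.5 points, SE = √[(0.08×0.92 + 0.04×0.96)/450] = 0.0158, and Φ(0.045/0.0158 − 1.96) = 81.4%. It does not bear on this point.

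**Which endpoints are affected.**

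| Endpoint | Competing event | Kaplan-Meier suitable for risk? |
|---|---|---|
| Composite (a) | none, all deaths count | yes |
| Total mortality (c) | none | yes |
| Cardiac mortality (c) | non-cardiac death | no |
| New intervention (d) | death from any cause, cardiac death included | no |

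**Formulas.** Let h be the hazard of the event and d the hazard of competing death, both assumed constant over T = 3 years.

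- One minus Kaplan-Meier: 1 − exp(−hT)
- Actual cumulative incidence: [h/(h+d)] × [1 − exp(−(h+d)T)]

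**Assumed inputs.** One minus Kaplan-Meier of 10%, so hT = −ln(0.90) = 0.1054. Competing mortality c of 5% to 20% at three years, so dT = −ln(1 − c).

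| c | (h+d)T | 1 − exp(−(h+d)T) | h/(h+d) | Actual incidence | Overstatement, points (relative) |
|---|---|---|---|---|---|
| 5% | 0.1567 | 0.145 | 0.6726 | 9.75% | 0.25 (2.5%) |
| 10% | 0.2107 | 0.190 | 0.5000 | 9.50% | 0.50 (5.3%) |
| 15% | 0.2679 | 0.235 | 0.3933 | 9.24% | 0.76 (8.2%) |
| 20% | 0.3285 | 0.280 | 0.3207 | 8.98% | 1.02 (11.4%) |

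For a Kaplan-Meier incidence of 5%, the actual values over the same range are 4.88%, 4.75%, 4.62% and 4.49%, an overstatement of 0.12 to 0.51 points.

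**Sensitivity to timing.** If all competing deaths fell soon after surgery, the actual incidence would approach (1 − c) times the Kaplan-Meier value. At c = 15% that is 0.85 × 10% = 8.5%, against 9.24% under constant hazards. Late competing deaths would shrink the overstatement.

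**Between arms.** Take the same event hazard in both arms (one minus Kaplan-Meier 10%) and competing mortality of 15% v 10%. Kaplan-Meier shows 10% v 10%, a gap of zero. The actual risks are 9.24% v 9.50%, a gap of 0.26 points. With 20% v 10%, the gap in actual risk is 9.50% − 8.98% = 0.52 points and the Kaplan-Meier gap is still zero. The Kaplan-Meier curves do not move. The actual risk moves, and with it the amount by which Kaplan-Meier overstates it.

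**The case against.** The strongest reply is that the Analysis section does not name these two endpoints. Its sentence on the 6-month and 3-year data cannot be meant literally for everything measured then, because quality of life and costs are also assessed at those times and Kaplan-Meier does not apply to them. The wording looks like a generic summary in a condensed article, and endpoint-level handling of competing events is commonly left to an analysis plan that is not shown. This stands in part. The prescription for the two endpoints is inferred from general wording, and silence about competing events would not be a finding. But the article does fix a time-to-event method, states it twice and without exception, and cardiac mortality and new intervention are time-to-event outcomes within its scope.

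A second reply is that a cause-specific display is legitimate and matches the log-rank test paired with it. This also stands as far as the test goes. It does not make one minus Kaplan-Meier a correct reading of absolute 3-year risk.

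A third reply is size. In the 15% v 10% example, the overstatement differs between arms by 0.26 points. With 450 per arm and risks near 9.4%, the standard error of a risk difference is √(2×0.094×0.906/450) = 1.9 points, so this is about 0.13 standard errors. The assumed 5-point mortality gap also exceeds the 4-point difference hypothesised for the whole 30-day composite. This stands: the effect is modest.

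A reader might infer that the Kaplan-Meier curves themselves shift with each arm's mortality, or that the method would create a spurious gap between arms. The calculation does not support either inference. With the event hazard held fixed the curves stay where they are, and in the example Kaplan-Meier shows no gap while the actual risks differ slightly.

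**Conclusion.** The point holds as a modest, cheaply corrected weakness in how two secondary endpoints would be displayed. As worded, the Analysis section applies Kaplan-Meier to cardiac mortality and to new intervention. If competing deaths are censored, one minus Kaplan-Meier overstates the actual cumulative incidence of both. Under constant hazards, a Kaplan-Meier incidence of 10% and competing mortality of 5% to 20%, the overstatement is about 0.25 to 1.0 percentage points. It would be larger if competing deaths cluster early. These rates are all assumptions, since the document states none.

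The point should not be carried further. The log-rank test remains valid as a comparison of cause-specific hazards, and nothing here touches the primary 30-day analysis, the composite during follow-up or total mortality.

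**What to change.** Amend the Analysis section so that the method follows the endpoint:

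- Keep Kaplan-Meier for the composite of death, stroke and myocardial infarction and for total mortality.
- For cardiac mortality, plot Aalen-Johansen cumulative incidence with non-cardiac death as the competing event. For new intervention, do the same with death from any cause as the competing event.
- Show the competing-death curve next to each, and report the 3-year risk difference between arms with its 95% CI.
- Keep the log-rank test for these two endpoints, labelled as a comparison of cause-specific hazards.

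The cost is a few lines of text and standard software. Dates of death and the records needed to review cause are already to be collected. No extra patients are needed. The downside is slightly lower reported incidences and one extra curve per endpoint.
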